## Abstract

**Background:**

Work capacity evaluations by independent medical experts are widely used to inform insurers whether injured or ill workers are capable of engaging in competitive employment. In many countries, evaluation processes lack a clearly structured approach, standardized instruments, and an explicit focus on claimants’ functional abilities. Evaluation of subjective complaints, such as mental illness, present additional challenges in the determination of work capacity. We have therefore developed a process for functional evaluation of claimants with mental disorders which complements usual psychiatric evaluation. Here we report the design of a study to measure the reliability of our approach in determining work capacity among patients with mental illness applying for disability benefits.

**Methods/Design:**

We will conduct a multi-center reliability study, in which 20 psychiatrists trained in our functional evaluation process will assess 30 claimants presenting with mental illness for eligibility to receive disability benefits [Reliability of Functional Evaluation in Psychiatry, RELY-study]. The functional evaluation process entails a five-step structured interview and a reporting instrument (Instrument of Functional Assessment in Psychiatry [IFAP]) to document the severity of work-related functional limitations. We will videotape all evaluations which will be viewed by three psychiatrists who will independently rate claimants’ functional limitations. Our primary outcome measure is the evaluation of claimant’s work capacity as a percentage (0 to 100 %), and our secondary outcomes are the 12 mental functions and 13 functional capacities assessed by the IFAP-instrument. Inter-rater reliability of four psychiatric experts will be explored using multilevel models to estimate the intraclass correlation coefficient (ICC). Additional analyses include subgroups according to mental disorder, the typicality of claimants, and claimant perceived fairness of the assessment process.

**Discussion:**

We hypothesize that a structured functional approach will show moderate reliability (ICC ≥ 0.6) of psychiatric evaluation of work capacity. Enrollment of actual claimants with mental disorders referred for evaluation by disability/accident insurers will increase the external validity of our findings. Finding moderate levels of reliability, we will continue with a randomized trial to test the reliability of a structured functional approach versus evaluation-as-usual.

## Background

Western countries have insurance systems in place that provide wage replacement benefits to individuals whose reduced health restricts or prevents them from working [1]. Over the last decade, most countries of the Organization for Economic Co-operation and Development (OECD) have experienced escalating rates of disabled workers, with current estimates ranging between 4 to 8 individuals per thousand of working age population per year [2]. In absolute terms, the number of new recipients of disability benefits per year ranges between 16,000 individuals for smaller countries like Switzerland and 1,700,000 for countries like the USA which constitutes a substantial economic challenge for society. Mental illness is currently the most common cause of disability from work [2–4].

Both public and private insurance systems commonly use medical evaluations conducted by independent health professionals to determine the functional capacities of workers who claim inability to work due to illness or injury [5–7]. The findings of these independent disability evaluations are highly influential, often determining whether or not a claimant receives wage-replacement benefits, and the amount of compensation. Expectations prevail that claimants with similar health impairments and similar work demands will receive similar judgments regarding their (in-)ability to work from medical experts. However, anecdotal evidence suggests that many evaluation reports are of poor quality [8] and that different experts attending the same claimants often disagree regarding their ability to work (Fig. 1) [9–14].

**Fig. 1 Fig1:**
[figure not shown]
The case: A 49 year old female clerk with recurrent depressive disorders and a current episode of depression of moderate severity (ICD 10-diagnosis: F33.1) underwent a medical evaluation for disability benefits. The evaluation was videotaped and – together with the clerk’s medical notes - circulated to 22 psychiatric experts with the request to provide a medical diagnosis and a judgment of her work capacity in her previous job. ([9], with permission of the publisher, Licence number 3764760136993). The German disability benefit system allocates claimants for disability benefits in one of three categories: able to work more than six hours = full work capacity; able to work between three and six hours = partial work capacity; able to work less than three hours = unable to work

A key criticism of disability evaluations is the failure of medical experts’ to clearly relate how claimants’ impaired health affects their ability to engage in competitive employment [14–18]. Rather, experts refer to their implicit professional expertise [11, 12, 19, 20]. This gap is prevalent in work capacity evaluations independent of the underlying health condition, and may be a fundamental source for variation between expert judgments and contribute to low reliability of work capacity evaluations.

In an effort to improve transparency and reliability, we developed a multi-facetted functional approach to work capacity evaluation, with a focus on the claimants’ functional deficits and their remaining functional capacities. We call this approach “functional evaluation”. Functional evaluation complements conventional psychiatric evaluations that psychiatric experts perform according to their personal routine (Fig. 2). Since structure and standardization improve reliability [21–25], a structured approach for eliciting work-related functional information from the claimants and a standardized reporting instrument for documenting experts’ findings are central components of the functional evaluation.

**Fig. 2 Fig2:**
[figure not shown]
Functional evaluation integrated in the conventional psychiatric assessment which is performed according to the personal routine of the psychiatric expert

The functional evaluation consists of a semi-structured interview with a focus on the claimants’ work, their self-perceived work (in-)capacity and their remaining ability to perform work-related tasks in relation to their health complaints; a detailed job description about the previous workplace obtained from the employer by the insurers and a selection of showcase jobs for suitable alternative work, and the Instrument for Functional Assessment in Psychiatry (IFAP) to document claimants’ functional capacities and limitations in common work-related activities [26].

The IFAP uses a structured semi-quantitative format to report the functional capacity of claimants (Fig. 3). First, psychiatrists report twelve key mental functions which are commonly affected in claimants with mental disorders (IFAP 1): temperament and personality, affability, psychic stability, openness towards new experience, self-confidence, mental energy, attention, memory, emotional function, thinking, higher cognitive functions, experience of self and of time. Each function is defined by the International Classification of Functioning, Disability and Health (ICF) [27] and rated on a 0 (no impairment) to 4 (completely impaired) scale with anchor definitions for the impairment ratings.

**Fig. 3 Fig3:**
[figure not shown]
Structure of the Instrument of Functional Assessment in Psychiatry, IFAP

**Fig. 4 Fig4:**
[figure not shown]
The RELY study. Recruitment and study flow

Second, the IFAP uses the Mini-ICF-APP [28] to report work-related functional capacities commonly impaired in claimants with mental disorders. The Mini-ICF-APP has been developed and validated in the German occupational rehabilitation setting [29–31]. It was recently translated and validated in a social psychiatry setting (single center secondary mental health care service) in the United Kingdom [32] and in a community mental health center in Italy [33]. The Mini-ICF-APP allows users to rate 13 work-related functional capacities: adherence to regulations, planning and structuring of tasks, flexibility, competency, endurance, assertiveness, contact with others, group integration, intimate relationships, non-work activities, self-care, mobility, and competence to judge and decide. Using a 0 (no limitations) to 4 (completely limited) scale, experts rate functional limitations associated with each item in reference to a detailed description of the previous job (IFAP 2a). To rate work ability in suitable alternative work, assessors select a reference job from a spectrum of showcase jobs in a large hotel which seems most suited to the claimants’ experience and remaining capacities, and rate in the same way any functional limitation for each of the 13-items in reference to the selected hotel job (IFAP 2b).

Finally, psychiatrists reflect on their ratings on the claimants’ mental functions and functional capacities. They estimate for how many hours the claimants should be able to work and their productivity before providing a judgment of the claimants overall work capacity on a scale from 100 to 0 % in the previous job and any suitable alternative job (IFAP 3). This judgment is used by disability insurers to calculate the amount of wage replacement benefits that will be paid to injured or ill workers through disability benefits.

The RELY-study [RELY stands for Reliability of Functional Evaluation in Psychiatry] will enroll patients with mental disorders claiming disability benefits and explore the inter-rater reliability of expert judgments regarding claimants’ work (in-) capacity based on a semi-structured functional interview and standardized reporting of work-related functional capacities. This study aims to demonstrate that the functional approach can achieve moderate reliability (ICC > 0.6) on work capacity evaluations in patients with mental disorders. The psychometric properties for the items of the three IFAP‐instruments (mental functions, activity limitations, work requirements) will show an interrater reliability above 0.5 for at least 85 % of the items, and above 0.65 for at least 20 % of the items. Justification of the thresholds: A recent study in social insurance addressing similar factors in claimants found that 6 raters evaluating ten items in twenty case vignettes reached an interrater reliability between 0.34 and 0.72 [34].

## Methods/Design

To optimize completeness and transparency in reporting the RELY study protocol, the structure and content of this manuscript was informed by the Guidelines for Reporting Reliability and Agreement Studies (GRRAS-guidelines) [35] Fig. 4.

### Study design

RELY will be a multi-center reliability study in which four psychiatric experts will independently assess workers undergoing a disability evaluation to assess restrictions and limitations associated with their mental illness.

### Setting

Consecutive claimants will be recruited from the Zürich office of the Swiss National Disability Insurance and from the Swiss National Accident Insurance Fund, Suva, while the evaluations and videotaping will be arranged through four independent assessments centers (two in Basel, one in Lucerne, and one in Interlaken).

### Participants

Medical and administrative staff at the insurance offices will identify and contact eligible claimants who have been scheduled to undergo a polydisciplinary disability evaluation, including a psychiatric evaluation. Eligible claimants will be workers whose first time disability evaluation includes a psychiatric interview, and capable of communicating in German without an interpreter. No other exclusion criteria apply.

After providing claimants with brief information about the study, the administrative staff will request permission to provide their name and telephone number to the research team so that they can be contacted about joining the RELY study. At that point, the insurer’s involvement in the study will end. Claimants who approve being contacted for the study will receive a detailed patient information that explains the study and its implications for the claimant in plain language. Next, a researcher will call to discuss the study with the claimants, to answer any questions that may have come up and to explain the informed consent form for participation. The claimants are then being asked to sign and return the informed consent form to the researcher. (For further details see Declarations, 2. Ethics approval and consent to participate).

### Interviewers and raters

Medical experts eligible for our study will be psychiatrists who currently provide disability evaluations for the Swiss National Disability Insurance or the Swiss National Accident Insurance acquired through a convenience sample of 20 psychiatric experts. No further eligibility criteria (such as level of expertise or years of experience) applied to reflect real life and prevent sampling error [2]. According to Swiss practice [36], the vast majority of experts are active in patient care. Participating psychiatrists will undergo a standardized, pre-piloted, training program for functional evaluation (see below [26]).

All psychiatric experts will conduct at least one videotaped disability evaluation and rate up to seven videotaped evaluations completed by their colleagues. They will be reimbursed for their time according to their usual rate. Psychiatrists and claimants will not be blinded to the study. Psychiatrists performing the evaluation will not be visible on the video, however, psychiatrists rating claimants shown in the videos may recognize voices of their colleagues.

### Training program in functional evaluation

Our functional evaluation approach focusses on the claimants’ health related functional limitations that relate to their ability to work, and complements psychiatrists’ conventional evaluation. The functional evaluation is consistent with the framework of the International Classification of Functioning, Disability and Health [27] and consists of the following components: 1) a semi-structured functional interview focusing on the claimants’ self-perceived limitations to work as a starting point for the evaluation; 2) a reporting instrument (IFAP) to document experts’ judgments with regards to the claimants’ mental functions (12 items) and their functional capacities (13 items); and 3) a detailed description of their last job and any suitable alternative work.

The training consists of written material describing the interviewing approach and information about the IFAP-instrument. Three face-to-face meetings lasting for three hours each will be used to discuss the functional evaluation with a methodological and a content expert based on cases from the experts’ own practice. Between training sessions, psychiatrists will be asked to use the functional evaluation with their own claimants and bring forward to the meetings any questions that arise. Additional details of the functional evaluation training program are described elsewhere [26].

### Procedures

#### The interview

The assessment centers will assign all enrolled study claimants to the next available study psychiatrist. Following a review of the claimants’ medical records provided by the insurer, experts will use the functional evaluation technique [26] to interview claimants. Interviews are anticipated to last 2 to 3 h, and will take place at an assessment center or the psychiatrist’s office.

The same research assistant will record all videos to ensure standardized recordings, using two cameras to prevent technical failures. Claimants will be filmed, but the assessing psychiatrist will remain off camera. The interviewing experts will write a psychiatric evaluation report for the insurer which will be integrated in the final polydisciplinary report. Psychiatrists who conduct the evaluation interview will provide a summary of the claimant’s socio-medical history for the rating psychiatrists who will review the video of the evaluation and complete study forms as detailed below.

Following the interview, and in the absence of the expert, the research assistant will provide the Questionnaire on Perceived Fairness to all claimants, with instructions that they can complete and return the form immediately, or later at home and return it to the research center in a sealed envelope.

The ratings: Three psychiatrist raters from a pool of 20 raters will be randomly allocated, via a web application, to each enrolled claimant. Randomization will prevent selection bias (e.g., the same three raters consistently forming a group [‘rater-group-membership’]) [37]. To avoid contamination, raters will be blinded to co-raters who view the same videotape [38, 39]. Four ratings will be generated for each enrolled claimant: one by their interviewing psychiatrist and three by psychiatrists who will independently review the video of the evaluation.

Psychiatrist raters will review videos of claimants’ evaluation interviews, their medical histories and job descriptions, and complete the IFAP-instruments through a secured website. All psychiatrists will receive information on how to access the secured website and standby support from the research team in case of unforeseen challenges with the data-security system.

### Data collection

Sociodemographic data on all eligible claimants (age, gender, civil status, nationalities and country of origin) and psychiatric experts (age, gender) will be recorded, complemented by psychiatrists’ professional experience (years since specialization; years working as psychiatric expert; number of work capacity evaluations over the last year; working concurrently as treating psychiatrist and psychiatric expert [Yes/No]). For eligible claimants who chose not to participate, insurance staff will record their mental disorder, gender and age.

Following each disability evaluation, the interviewing psychiatrist and three psychiatric raters will record all mental disorders that impact on work capacity using ICD 10 coding. They will fill in the IFAP-instrument, thereby providing estimates and judgments on overall work capacity related to the claimants’ previous job and to suitable alternative work (single item on a scale from 100 to 0 %, higher values indicate better work capacity), and on the following variables: commonly affected mental functions (12 items on a 5-point scale, higher score indicate greater impairment) and functional capacities commonly affected in mental disorders, also related to the claimants’ previous job and to suitable alternative work (13 items on a 5-point scale, higher scores indicate greater impairment).

Each psychiatrist who completes a disability evaluation will rate their certainty regarding the claimant’s overall work capacity (scale from 0 to 10, higher scores indicate greater certainty), the severity of the claimants’ mental disorder(s) compared to that of other claimants with similar mental disorders (scale from 0 to 10, higher scores indicate greater severity), and the extent to which claimants in the study represent ‘typical claimants’ referred for disability evaluation.

Six criteria capture ‘typicality’ in the context of our study: severity of mental disorders, complexity of diagnoses, impact of the claimants’ mental disorders on work capacity, work trajectory, spectrum of jobs and occupational activities, and education and professional training. For each criterion, respondents will relate the current claimant to other claimants assessed in their practice, report the frequency of evaluating such a claimant on a 3-item scale (seldom/neither seldom nor often/often) and generate a global judgment on the frequency of encountering such a claimant (same 3-item scale).

#### Perceived fairness of the evaluation process

The Questionnaire on Perceived Fairness of the evaluation process is based on a similar validated questionnaire used in the Dutch National Disability Insurance [40]. This instrument is comprised of 30 items on topics such as the experts’ perceived level of preparedness for the interview, their explanations about the encounter and the next steps following the interview, comprehensiveness of the interview, opportunities for the claimants to respond and ask questions, and attention and respectful demeanor towards the claimant, with response options on a 5-point scale (higher scores indicate higher agreement with the statement) and one item on the general satisfaction with the psychiatric evaluation (10-point scale, higher scores indicate higher satisfaction). Immediately following an evaluation, we pretested the questionnaire with 33 claimants for comprehension, length, ease to use, acceptance, and made modifications according to feedback, such as simplifying the wording of some questions [41].

#### Psychiatrists’ perceptions of the functional evaluation process

A semi-structured telephone interview will compile the psychiatrists’ perceptions on the functional evaluation. They will rate the usefulness of all three components of the functional evaluation for reaching a global judgment on claimants’ work capacity in the previous job and any suitable alternative work. They will report to what extent they integrated the functional interviewing (all parts of the interview/some parts, and listing those/none) and the various components of the IFAP-instrument (mental functions/functional capacities/descriptions of suitable alternative work/nothing) in their routine of work capacity evaluation outside of the study.

### Sample size

Our primary outcome is psychiatrists’ global rating of work capacity (expressed as percentage work capacity) in the previous job and in suitable alternative work. The intra-class correlation coefficient (ICC) should be at least 0.6 to be useful [42], which seems achievable in the insurance medicine context. [43, 44] With a sample size of 30 claimants, each evaluated by four raters, we expect to estimate an assumed ICC of at least 0.6 with a precision expressed as the width of a two sided 95 % confidence interval (CI) of ± 0.15 [45].

In an exploratory analysis, we will assess which variables – clinical (diagnoses), professional (psychiatrists’ characteristics) and demographic (claimants’ characteristics) – are associated with variation in the reliability of expert judgments, although we anticipate that these analyses will be underpowered to detect significant associations.

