### Statistical analysis

We will describe psychiatrist and claimant characteristics with absolute and relative frequencies for categorical variables and with mean and standard deviation, or median and interquartile range, for continuous variables. To explore whether random allocation of psychiatrists to claimants was successful, i.e., producing low rater-group-membership, we will calculate the frequency of the same two, three or four psychiatrists being allocated to a claimant (‘rater-group-membership’) and calculate the Jaccard similarity coefficient of each pair of psychiatrists.

Each rating (rather than a consensus rating) will be used for our analysis. To estimate the means and associated 95 % CIs for the primary and secondary outcomes we will use mixed-effects models that take into account the crossed cluster design (i.e., each psychiatrist will assess several claimants and each claimant will be assessed by several psychiatrists) by including crossed random intercepts for claimants and psychiatrists, if appropriate, in order to obtain adjusted standard errors [46].

Furthermore, we will use mixed-effects models to estimate the variance components needed for the computation of the ICCs of work capacity, IFAP items and IFAP item sums (i.e., the residual variance and between-claimant variance for the ICC_absolute agreement_, and additionally between-psychiatrist variance for the ICC_consistency_) [47]. The associated measures of precision (95 % CIs) will be obtained by model-based parametric bootstrapping. Additionally, we will perform exploratory subgroup analyses on the ICCs for work capacity for specific diagnostic groups (ICD 10 categories of mental disorders, F00-F09; F10-F19; F20-F29; F30-F39; F40-F48; F50-F59; F60-F69). The clinical interpretation of ICC and agreement will follow the criteria by Fleiss [48] and Cicchetti [49]. For the ICC: poor (ICC < 0.4); fair (0.40 to 0.59); good (0.60 to 0.74); excellent (0.75 to 1.00), for the level of percentage agreement: poor (<70 %); fair (70 % to 79); good (80 to 89 %); excellent (>90 %).

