Little prior knowledge exists about the processes of usual psychiatric evaluations: How do experts sort the collected information? What are their implicit criteria to select certain information and discard others? What weights do they attribute to the information selected, which makes some information more relevant than others? An optimal research program on disability evaluation would have started by understanding the processes and their relative impact on the critical outcomes before studying the critical societal and patient related outcomes. This approach, however, would have lasted two decades and longer with uncertain results. We therefore used the experience and opinions from our expert group to fill the many gaps we encountered in the design of the study, fully aware of the importance but also limitations of expert advice.

While we expect the sample size to have enough power for measuring the pre-specified reliability with pre-specified precision, it will lack power to detect significant effects when analyzing the evaluation process and predictors for work capacity. These analyses will therefore only inform about trends, they may, however, help in the planning of future studies. Multiple imputation assumes that data are missing at random, and the complete case analysis assumes missing completely at random. Missing data may not be missing at random, a condition that no statistical analysis can address.

Limiting the study to German speaking claimants will exclude many migrants with insufficient language skills who represent a substantial proportion of people applying for work disability.

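### At the planning ICC of 0.60, 30 claimants with four ratings each give a 95 % CI of about ±0.165, not the stated ±0.15

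*Protocol article*

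**What the plan says.** The Sample size section fixes every input to the precision claim. The design is "With a sample size of 30 claimants, each evaluated by four raters", the planning value appears in "we expect to estimate an assumed ICC of at least 0.6 with a precision expressed as the width of a two sided", and the target is the "width of a two sided 95 % confidence interval (CI) of ± 0.15". A reference is cited for the method, but no formula is shown. The Limitations section relies on the same figure without repeating the number: "While we expect the sample size to have enough power for measuring the pre-specified reliability with pre-specified precision".

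Two features of the design bear on the side issue of variance between psychiatrists. The Procedures section says "Three psychiatrist raters from a pool of 20 raters will be randomly allocated, via a web application, to each enrolled claimant", and the interviewing psychiatrist adds the fourth rating. Under Interviewers and raters, each psychiatrist is to "conduct at least one videotaped disability evaluation and rate up to seven videotaped evaluations completed by their colleagues". The Statistical analysis section estimates outcome means "by including crossed random intercepts for claimants and psychiatrists, if appropriate". For the ICCs it names residual and between-claimant variance for absolute agreement, and adds between-psychiatrist variance for consistency.

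**The concern.** The precision statement is the only quantitative justification for enrolling 30 claimants. All of its inputs are given, so it can be recomputed, and the usual formulas return a wider interval at the planning value. A reader who takes ±0.15 at face value expects an observed ICC of 0.60 to come with a lower limit of 0.45. The study aims to show an ICC above 0.6 and to go on to a randomized trial if reliability is moderate, so how tightly 0.60 is pinned down is relevant to how the result will be read.

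**Working it through.** **Inputs.** From the Sample size section: n = 30 claimants, k = 4 ratings, ICC ρ = 0.60, two-sided 95 % (z = 1.96). The ±0.15 is read as a half-width, so a full width of 0.30. This is the reading most favourable to the plan.

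**1. Large-sample formula.** Half-width = z·√[2(1−ρ)²(1+(k−1)ρ)² / (k(k−1)(n−1))].

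- (1−0.6)² = 0.16; (1+3×0.6)² = 2.8² = 7.84; k(k−1)(n−1) = 4×3×29 = 348.
- 2×0.16×7.84/348 = 0.00721; square root 0.0849; times 1.96 = **0.166**.

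**2. Exact one-way F interval at an observed ICC of 0.60.** The F ratio is (1+3×0.6)/(1−0.6) = 2.8/0.4 = 7, with 29 and 90 degrees of freedom.

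- Lower: 7/1.741 = 4.020; (4.020−1)/(4.020+3) = 0.430.
- Upper: 7×1.911 = 13.377; (13.377−1)/(13.377+3) = 0.756.
- Half-width = (0.756−0.430)/2 = **0.163**.

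**3. Does any standard variant return 0.15 with n = 30, k = 4, ICC 0.60 and 95 %?**

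| Variant | Half-width |
|---|---|
| Large-sample, n in place of n−1 | 0.164 |
| Fisher-transformed (0.414 to 0.747) | 0.167 |
| Two-way consistency F (0.429 to 0.756) | 0.163 |
| Expected exact-F width, simulated | 0.162 |

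None does. In the simulation behind the last row, about 24 % of studies had a half-width of 0.15 or less. Changing a stated input does not recover 0.15 either: a 90 % interval gives 0.140, five ratings 0.157, three ratings 0.185.

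**4. Claimants needed for ±0.15 at ICC 0.60.**

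- Large-sample: n = 8z²(1−ρ)²(1+(k−1)ρ)²/(k(k−1)w²) + 1 with w = 0.30, so 8×3.8415×0.16×7.84/(12×0.09) + 1 = 36.7, that is 37.
- Exact F: the half-width is 0.1508 at n = 35 and 0.1487 at n = 36, so 36.

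**5. ICC at which 30 × 4 reaches ±0.15.**

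| ICC | Large-sample | Exact F |
|---|---|---|
| 0.60 | 0.166 | 0.163 |
| 0.65 | 0.153 | 0.150 |
| 0.66 | 0.1505 | 0.148 |
| 0.67 | 0.148 | 0.145 |
| 0.70 | 0.138 | 0.136 |

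The stated figure holds from an ICC of about 0.65 (exact F) or 0.66 (large-sample) upwards.

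**6. Variance between psychiatrists.** The article gives no value, so its share of total variance is an assumption, varied here from 0 to 30 %. There are 120 ratings from 20 psychiatrists, six each on average.

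- Crossed model, absolute-agreement ICC 0.60, information-based half-width at shares of 0/5/10/15/20/25/30 %: 0.166/0.165/0.165/0.166/0.169/0.174/0.180.
- Crossed model, consistency ICC 0.60: 0.169, rising to 0.174.
- One-way estimator without a psychiatrist term, simulated 95 % sampling half-range at 0/10/20/30 %: 0.168/0.174/0.183/0.201. This is a different yardstick from a confidence interval half-width: it is already 0.168 with no psychiatrist variance, so only the increase from that base reflects psychiatrists.

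**The case against.** The best defence is the wording: the plan says at least 0.6, and ±0.15 is met over most of the range above 0.6. That is true from about 0.65 upwards. But precision is poorest at the bottom of the range, so a claim made for 0.6 and above has to hold at 0.6, which is also the planning value. Rounding does not help, since 0.163 to 0.166 does not round to 0.15. The cited source cannot be consulted here, so the approximation actually used is unknown, but no standard one tried returns 0.15.

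The defence is stronger on importance. This is a planning expectation in an estimation study. The Sample size section attaches no test or decision rule to ±0.15, and the reported intervals will come from parametric bootstrapping, so the planning figure cannot bias the result. All of this stands.

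Three stronger readings may tempt a reader, and the article does not support them.

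- **That psychiatrist variance must widen the interval further.** This depends on the estimator and on a share the article does not give. In the crossed model, absolute agreement shows no widening up to a share of about 15 %. Nor is ±0.18 a ceiling, since the one-way simulation reaches 0.201 at 30 %.
- **That the true interval falls into the article's poor band (below 0.40).** The lower limit moves from 0.45 to 0.43, and both are in the fair band (0.40 to 0.59).
- **That ±0.15 means a total width of 0.15.** The word width allows it, and it would need 144 claimants, but the ± sign points to a half-width.

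**Conclusion.** Wrong as written; a minor correction. With 30 claimants, four ratings each and an ICC of 0.60, the 95 % half-width is 0.163 to 0.166 against the stated 0.15, an excess of 0.013 to 0.016 (9 to 11 % of the stated figure). Equivalently, the plan is six to seven claimants short of the 36 to 37 that ±0.15 would need. This rests on reading ±0.15 as a half-width and on standard one-way or two-way ICC intervals. The conclusion does not depend on any assumption about psychiatrist variance: no scenario examined brings the half-width down to 0.15 at an ICC of 0.60. The shortfall does not invalidate the design, change any interpretive category or show that more claimants are required.

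**What to change.** Keep 30 claimants and restate the figure in the Sample size section, for example: *With 30 claimants and four ratings each, an ICC of 0.60 is estimated with a 95 % CI of about ±0.17 (0.43 to 0.76); ±0.15 is reached for an ICC of about 0.66 or above.* Name the formula used, so that the figure can be reproduced. The mention of pre-specified precision under Limitations then refers to the restated figure and needs no number of its own.

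If psychiatrist variance is mentioned, make it conditional: the interval may be somewhat wider if psychiatrists differ systematically, depending on the estimator and the assumed share.

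The cost is one or two sentences and a slightly less favourable stated precision. Enrolment, design and analysis are unchanged.
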